## Abstract

**Background:**

Because of an expected shrinking supply of medical doctors for hospitalist posts, an increased emphasis on efficiency and continuity of care, and the standardization of many medical procedures, the role of hospitalist is increasingly allocated to physician assistants (PAs). PAs are nonphysician clinicians with medical tasks. This study aims to evaluate the effects of substitution of hospital ward care to PAs.

**Methods/Design:**

In a multicenter matched controlled study, the traditional model in which the role of hospitalist is taken solely by medical doctors (MD model) is compared with a mixed model in which a PA functions as a hospitalist, contingent with MDs (PA/MD model). Twenty intervention and twenty control wards are included across The Netherlands, from a range of medical specialisms. Primary outcome measure is patients’ length of hospital stay. Secondary outcomes include indicators for quality of hospital ward care, patients experiences with medical ward care, patients health-related quality of life, and healthcare providers’ experiences. An economic evaluation is conducted to assess the cost implications and potential efficiency of the PA/MD model. For most measures, data is collected from medical records or questionnaires in samples of 115 patients per hospital ward. Semi-structured interviews with healthcare professionals are conducted to identify determinants of efficiency, quality and continuity of care and barriers and facilitators for the implementation of PAs in the role of hospitalist.

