### Sample size calculation

To detect a relative difference in LoHS of 20% between the mixed ‘PA/MD model’ and solely ‘MD model’, assuming an average LoHS of 7 days [30], alpha 5%, power 80% and an ICC of 0.06 for patients in same ward, 40 wards including 100 patients each are required. Taking into account an expected drop-out rate of 10% at the level of wards, and a 10% drop out rate of patients (withdrawal of informed consent), 44 wards (22 in each arm) with each 115 patients are included. The number of in depth interviews depends on the moment data saturation is attained.

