### Data analyses

To compare hospital wards utilizing a mixed ‘PA/MD model’ with wards utilizing a solely ‘MD model’, we use logistic regression analyses for dichotomous outcomes and linear regression analysis for continuous outcomes, both with random coefficients to account for statistical clustering of data in hospital wards. The analysis is on an intention to treat basis and matching will be taken into account. Missing values are substituted by multiple imputation techniques. Multivariable models are constructed to correct for potential confounders. Covariables are included in the final model only if they modify the regression coefficient of ward care model (i.e. the central determinant) by more than 10% (regardless of statistical significance of effects). Explorative subgroup analyses per medical specialism will be conducted for each set of at least six wards with similar specialism are included. All estimates are calculated with 95% confidence intervals.

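### The article gives two different numbers of included wards, 40 in the abstract and 44 in the sample size section; if 40 is the recruited number, the planned 10% ward loss lowers power from 80% to about 76%.

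*Protocol article*

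**What the plan says.** The abstract, under Methods/Design, states: "Twenty intervention and twenty control wards are included across The Netherlands". The same paragraph says that most measures are taken in "samples of 115 patients per hospital ward".

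The section Sample size calculation works in two steps. It first gives the number needed for analysis: "40 wards including 100 patients each are required". This rests on a 20% relative difference in length of hospital stay, "assuming an average LoHS of 7 days", and "alpha 5%, power 80% and an ICC of 0.06 for patients in same ward". It then allows for 10% drop-out of wards and 10% drop-out of patients, and concludes: "44 wards (22 in each arm) with each 115 patients are included".

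In that section, 40 wards go with 100 patients (before drop-out) and 44 wards go with 115 patients (after drop-out). The abstract has 40 wards with 115 patients, a combination that the sample size section does not contain.

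**The concern.** Both places describe the wards that are included in the same study, and they give different counts. In a ward-level comparison with an intraclass correlation of 0.06, power depends mainly on the number of wards and only weakly on the number of patients in each. The four wards in dispute are exactly the reserve that the plan sets aside for ward drop-out. If the sample size section is right, the reserve exists and the 80% power claim is sound. If the abstract is right, there is no reserve, and the claim holds only if no ward is lost, although the plan itself expects to lose one in ten. A reader who wants to judge recruitment against the plan cannot tell which number to use.

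**Working it through.** **Inputs.** From Sample size calculation: 40 wards (k = 20 per arm) of m = 100 patients for 80% power; alpha 5%, taken as two-sided because the article does not say; ICC 0.06; mean stay 7 days and a 20% difference, so 7 × 0.20 = 1.4 days; 10% of wards and 10% of patients lost; 44 wards of 115 patients included. From the abstract: 20 + 20 wards, 115 patients each.

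**Step 1: the plan's own figure.** The design effect is 1 + (m − 1) × ICC = 1 + 99 × 0.06 = 6.94. Each arm has 20 × 100 = 2000 patients, an effective 2000 / 6.94 = 288.2. The standard deviation is not stated. Solving for the one that gives 80% power: SD = 1.4 × √(288.2 / 2) / (1.96 + 0.8416) = 6.0 days. This shows that 40 × 100 is coherent with a round SD. It is back-solved, so it does not independently confirm the figure.

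**Step 2: drop-out allowances.** Wards: 40 × 1.1 = 44, and 44 × 0.9 = 39.6. Patients: 115 × 0.9 = 103.5, which covers the 100 needed.

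**Step 3: power after the planned ward loss.** At 80% power the standardised effect is 1.96 + 0.8416 = 2.80. With cluster size fixed it scales with the square root of the number of wards, so the SD cancels:

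power = Φ(2.80 × √(wards remaining / 40) − 1.96)

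- 44 recruited, 39.6 remain: Φ(2.80 × √0.99 − 1.96) = 79.6%.
- 40 recruited, 36 remain: Φ(2.80 × √0.90 − 1.96) = Φ(0.70) = 75.7%.

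**Step 4: allowing for the actual patients per ward.** For m other than 100, the ratio under the root is also multiplied by [m / (1 + (m − 1) × 0.06)] / [100 / 6.94].

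| Wards recruited | Wards remaining | Patients per ward | Power |
|---|---|---|---|
| 44 | 39.6 | 103.5 | 79.8% |
| 40 | 36 | 100 | 75.7% |
| 40 | 36 | 103.5 | 75.9% |
| 40 | 36 | 115 (no patient lost) | 76.5% |

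Extra patients per ward do not make up for lost wards.

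**Step 5: sensitivity.** Using a t reference with the SD recalibrated so that 40 × 100 again gives 80% (SD 5.85 days), 36 wards give 75.5% to 75.7%. With one-sided alpha the result is about 76%.

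**The case against.** The best defence is that the abstract reports the wards required and the sample size section the wards recruited. That would be a normal condensation, but the abstract's 115 patients per ward rules it out: a consistent statement of the requirement would have given 100.

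A second defence is that the sample size section is the operative statement and does provide a reserve. This stands as far as it goes. If 44 is the recruited number, the design keeps its power to within half a percentage point and only the abstract needs correcting. The loss to about 76% is conditional on 40 being right.

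Three stronger readings are tempting and are not supported:

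- A reader might infer that a ward that drops out takes its matched partner with it, so that 44 wards leave about 18 complete pairs. The article does not say so. The section Data analyses says only that "matching will be taken into account", within regression models with random coefficients for clustering in wards. Such a model can keep an unpaired ward. How unpaired wards are handled is detail that an article commonly leaves to the analysis plan.
- A reader might call the inflation to 44 an error, since 40 / 0.9 = 44.4. The shortfall is 0.4 of a ward, and power is still 79.6% to 79.8%. Nothing turns on it.
- A reader might quote 78% for 40 wards and 73% for 36 from a t reference at an SD of 6.0 days. Those figures combine an SD calibrated on the normal formula with a t distribution and so overstate the loss; Step 5 gives the consistent version.

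**Conclusion.** The point holds as a contradiction about the size of the study: the abstract and the sample size section give 40 and 44 included wards, and the abstract mixes figures from before and after drop-out. It should be corrected because the number of wards governs power for the primary outcome.

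The consequence depends on which number is true: about 80% with 44 recruited, about 76% with 40. The 76% assumes that 40 wards of 100 patients do give 80% power, as the article states, that wards are lost at the planned 10%, and that unpaired wards stay in the analysis. Given the first of these, it does not depend on the SD. The documents do not support the wider conclusion that the design misses its stated power; as set out in the sample size section, it meets it to within half a percentage point.

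**What to change.** State one recruited number of wards in both the abstract and Sample size calculation.

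- If it is 44, change the abstract to 22 intervention and 22 control wards. The patient number there, 115, already agrees.
- If it is 40, change the sample size section to say so, and restate the power as about 76% after the planned 10% ward loss (36 wards).

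This is a change of text. It needs no extra recruitment and no change to the design or analysis. The only downside arises in the second case, where the stated power becomes slightly less favourable.

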**Discussion:**

Findings from this study will help to further define the role of nonphysician clinicians and provides possible key components for the implementation of PAs in hospital ward care. Like in many studies of organizational change, random allocation to study arms is not feasible, which implies an increased risk for confounding. A major challenge is to deal with the heterogeneity of patients and hospital departments.

**Trial registration:**

ClinicalTrials.gov ID NCT01835444

## Introduction

### Background

Healthcare systems across the world face a number of challenges, such as a rising demand for healthcare services, a growing number of chronic ill patients and rising patient expectations. Concurrently, the supply of medical doctors (MDs) is constrained in most countries, leading to workforce shortages [1]. Nonphysician clinicians have been introduced into the medical domain in order to take over tasks from MDs [2]. An example of a nonphysician clinician is the Physician assistant (PA), a health care professional licensed to practice medicine in defined domains, in collaboration with MDs but with a substantial degree of professional autonomy [3]. PAs obtain medical history, perform physical examinations, request and interpret additional testing, render medical diagnoses and treatment procedures, and prescribe medication. They also perform specific medical procedures, such as endoscopies, catheterizations, elective cardioversion and minor surgeries [3,4]. In addition, PAs contribute to the quality of care by developing protocols, initiate or participate in quality projects and education programs [5].

The PA was first introduced in the sixties in the United States and then rapidly spread across the country [4]. In the Netherlands, the first PAs were introduced in 2001 [6,7]. Currently approximately 630 graduated PAs are employed in the Dutch healthcare system, on a total of about 65 000 registered physicians [8]. In the next few years, about 120 PAs will yearly complete their Master program. Contrary to the USA, where the majority of PAs work in primary care settings, most Dutch PAs (about 75%) work in the hospital settings [9]. The majority works at general surgery, surgical subspecialties, cardiology, anesthesiology or internal medicine [10]. The main features of Dutch PA’s are [7,10]:

• PAs follow a 30 month training program at a Master’s degree level.

• The Dutch PA programs incorporate a dual work-education model, which means that students are employed within a particular medical specialty while enrolled in the master’s PA program. The students undertake didactic and clinical education within this medical specialty from the beginning till the end of the curriculum.

• PA students are professionals with a health care-related bachelor’s degree and at least 2 years of clinical work experience in the health care domain.

• PAs conduct low to moderately complex medical tasks within a certain specialty, both in primary and secondary care. Most PAs practice in the hospital setting.

• Since January 2013, PAs are authorized to indicate and perform predefined medical procedures and subscribe medication without supervision. The scope of practice will be re-evaluated in 2017.

• Physician Assistant is a protected title by law. The legislation is written in the Individual Health Care Professions Act (Wet BIG), article 36a.

Since the first introduction of the PA, several studies have examined their performance. This body of evidence suggests that PAs can provide high-quality care in a large range of medical disciplines [11-14]. The studies indicate that they provide care that is comparable to that of MDs, with high levels of patient satisfaction [15-18]. Although there is international evidence for both efficacy and effectiveness supporting the reallocation of care from MDs to PAs, current research does not cover all settings and professions [2,13]. Many studies concern primary and critical care settings, while studies assessing the effects of substitution of non-acute inpatient medical care are limited. Some studies show methodological limitations like single centered, non-randomized, a relatively small sample size or no control condition. Besides, concerns have been expressed regarding potential adverse effects of involving PAs, such as negative impacts on patient safety and continuity of healthcare delivery.

In this study we focus on patients admitted to a hospital, who are taken care by a hospitalist. Hospitalists are responsible for the coordination of the daily medical care of hospitalized patients [19]. This role has traditionally been fulfilled by medical residents (MRs) and occasionally by medical specialists. In recent years, the role of hospitalist has been increasingly reallocated to PAs [3,11], facilitated by technological innovations and the standardization of many medical procedures by clinical protocols [20,21]. In 2013, approximately 200 graduated PAs were employed as hospitalist in the Netherlands. When PAs are employed as hospitalists, the applied model to cover 24/7 ward care is often a mixed model that contains both PAs and MDs as hospitalist, comprising a patient medical care team. The tasks of PAs in such a team are comparable to those of the MDs. The PAs, however, tend to work during daytime on weekdays, while MDs often work during evenings, nights and weekends. It is anticipated that within the next decades PAs will be increasingly employed in the management of hospitalized patients for a range of different specialism. However, empirical evidence about the consequences of reallocating medical ward care from MDs to PAs for the quality and safety of care is currently limited.

### Study aim

The primary aim of this study is to determine the effectiveness of hospital ward care by MDs compared to a patient medical care team consisting of both PAs and MDs. It is hypothesized that due to reallocation of care to a fixed number of PAs per hospital ward, inpatient care becomes more standardized and continued resulting in improved care, which will be reflected by shorter hospital stay. To measure effectiveness we therefore choose length of hospital stay (LoHS) as primary outcome measure. Besides the effectiveness, also the effects on quality and continuity of care and patient and care provider experiences are investigated.

## Methods/Design

### Study design and population

A multicenter non-randomized matched-controlled study is performed in The Netherlands, comparing wards utilizing a mixed ‘PA/MD model’ (intervention group) with wards utilizing a solely ‘MD model’ (control group, usual care). Control wards are matched with the intervention wards on the basis of medical specialism and hospital type (i.e. academic versus non-academic). Data collection runs parallel for each pair of matched intervention and control ward, with a maximum deviation of two weeks.

### Study setting

Hospital wards are being assigned to the intervention group if the PA has completed an accreditated master’s PA degree and covers at least 51% of the available ward care hours per week during dayshifts (8 h-18 h) on weekdays. Wards are assigned to the control group if solely MDs fulfill the hospitalist position. Exclusion criteria at ward level are: 1) Nurse practitioners (including in training) in the role of hospitalist; 2) Only non-graduated PAs in the role of hospitalist; 3) Psychiatric and pediatric wards and intensive care units. In order to enhance the generalizability of findings we include a heterogeneous sample of hospitals across the country and a mix of medical specialism.

### Study population

The focus of this study is on the patients admitted to the included hospital wards. Exclusion criteria at patient level are: 1) Patients younger than 18 years; 2) Terminally ill patients; 3) Patients in daycare. Daycare is defined as hospital admissions which are intended to last 24 hours or less. For patients who are not able to fill in questionnaires (e.g. patients with cognitive impairment), family relatives are asked to fill in the questionnaires. Besides the patients, also the PAs, MDs, and a sample of ten nurses who are employed at the included ward are involved as study objects. The sample of nurses is established by selecting the first ten nurses who are scheduled for a dayshift during the third week from data collection.

### Primary outcome

LoHS is the primary outcome measure. Reducing LoHs is important for payers of healthcare and for many patients. LoHS is defined as the time period in days between date of discharge and date of admission. To control for discharge delay for nonmedical reasons, i.e. delay attributable to waiting times for a place in a nursing home or a rehabilitation clinic, or help in the patient’s own home, we also register the date of completion of medical treatment in the hospital.

### Secondary outcomes

#### Quality of hospital ward care

To assess the quality of ward care, a set of eleven global clinical and process indicators has been selected from the literature and suggestions by a physician panel. The clinical indicators were derived from a national set of indicators for quality of hospital care from the Dutch Health Care Inspectorate (IGZ) [22]. All indicators cover a period of maximum one month after discharge. The selected indicators are:

Clinical indicators:

• Inhospital mortality

• Unplanned transfer to intensive care unit

• Cardiopulmonary resuscitation

• Pressure sore developed during admission

• Fever: number of days body temperature ≥38

• Pain score: number of days Numeric Rating Score ≥7

• Hospital infections: infusion-, urinary track-, airway-, and postoperative wound infections

• Presentation at department of emergency, within one month after discharge

• Non-elective readmission within one month after discharge

Process indicators:

• Days between discharge and letter of discharge

• Introduction hospitalist to the patient less than 24 hours after hospital admission

Data about unplanned readmission and presentation at emergency department after discharge are collected using self-administered patient questionnaires, which are send at one month after discharge date. Information about the other indicators will be retrospectively derived from patient medical records.

#### **
*Patients health-related quality of life*
**

Generic health-related quality of life is measured with the Euroqol-5D (EQ-5D), which is a widely used validated questionnaire containing five domains: mobility, self-care, usual activities, pain, and anxiety/depression [23]. Each domain has three possible levels indicating; no problems, moderate problems or sever problems. Besides, respondents are asked to value their overall health status on a visual analog scale, ranging from 0 (defined as the worst imaginable health state) to 100 (defined as the best imaginable health state). The EQ-5D is assessed by patient questionnaires at three time points: at admission, discharge and one month after discharge.

#### **
*Patient experiences with medical ward care*
**

Patient experiences with medical ward care are assessed by a self-administered questionnaire at discharge. This questionnaire focuses on satisfaction with communication, experienced continuity of care and cooperation, and the patients view on the medical competencies of the hospitalist. Patient perceptions on communication skills of the hospitalist are measured with the Communication Assessment Tool (CAT), which consists of 15 questions and can be rated on a 5 point Likert scale, ranging from ‘poor’ to excellent’. Although not validated in the Netherlands, the CAT has already proven to be a reliable and valid instrument in the hospital setting in the US [24]. Three subscales from the ‘Chronically Ill Patients Evaluate general Practice’ (CEP) questionnaire were added to measure the items satisfaction with continuity of care, cooperation of ward care providers, and medical competencies of the hospitalist [25]. Each item will be rated on a six point Likert scale, ranging from ‘poor’ to ‘excellent’. As this questionnaire has only been validated for primary care, psychometric properties will be examined in this study. To ensure that patients know who their hospitalist is, we include photos from the hospitalist(s) in the questionnaire. To assess whether patients understood the questions asked in the self-administered questionnaires, we pre-tested the questionnaire in a sample of ten patients admitted to two hospital wards in different hospitals.

#### **
*Health professionals’ work experiences and job characteristics*
**

An online questionnaire is compiled to measure job satisfaction, distress outcomes and other job characteristics of the care providers working at the included hospital wards; i.e. all MDs and PAs who fulfill the role of hospitalist, and a random sample of ten nurses in each of the participating wards.

*Job satisfaction* is assessed with the McCranie Job Satisfaction Scale, which consists of 13 questions which can be rated on a 6-point Likert scale, ranging from very dissatisfied to very satisfied [26]. The questionnaire addresses satisfaction with the amount of time which is available per patient, satisfaction with the level of work challenge, and satisfaction with the collaboration with nurses, medical specialists and medical residents. Some items were rephrased to make them appropriate for the specific profession of our interest and some questions were added. For all professions we additionally ask about satisfaction with collaboration with PAs. Besides, in the questionnaire for medical specialists a question about satisfaction with time spend on supervision was added, and in the questionnaire for hospitalists we additionally ask for satisfaction with the received supervision. Finally, respondents are asked to value their overall job satisfaction on a visual analog scale, ranging from 1 (extremely unsatisfied) to 10 (extremely satisfied).

*Job stress* is assessed by the 12-item General Health Questionnaire (GHQ-12). The GHQ-12 is a unidimensional, validated scale which comprises questions regarding anxiety, depression, social dysfunction, and loss of confidence. Statements are rated on a 4-point rating scale (symptom present: “not at all” = 0, “same as usual” = 0, “more than usual” = 1, and “much more than usual” = 1) GHQ-12 scores range from 0 to 12 with a higher score indicative of poorer psychological well-being [27].

*Workload* of hospitalists is measured in terms of number of patients seen per day and weekly overtime hours. We ask hospitalists (both PAs and medical residents) and medical specialists for the number of hours per week spend on both direct and indirect patient contacts at the hospital ward, and the number of hours per month spend on non-patient related tasks like participating in quality and patient safety projects and performing scientific research. In the questionnaire for hospitalists we additionally ask for the number of hours spend on patient related non-hospitalist tasks like performing medical procedures or supporting outpatient care. Besides, we ask the hospitalists how much supervision time they obtain, and the medical specialists how many time they spend on supervision.

#### **
*Continuity of care*
**

Effects of substitution of hospital ward care on patient experienced continuity of care are measured by a set of questions in the patient questionnaire at discharge, as described in the section ‘patients experiences with medical ward care’. Additionally, continuity of care is established by evaluating work schedules. All hospitalists are asked to fill in their real work schedule during fixed weeks: week 3, 7, 11 and 15 after the start of the inclusion of patients. Continuity of care will be assessed by counting the number of rotations in the hospitalist position during these fixed four weeks. Data collection runs parallel for each pair of matched intervention and control ward.

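### The fever-day and severe-pain-day indicators do not separate symptoms present on arrival from those arising on the ward, and the admission values are not among the planned covariates

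*Protocol article*

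**What the plan says.** The section Quality of hospital ward care in the protocol article states the purpose of the list: "To assess the quality of ward care, a set of eleven global clinical and process indicators has been selected". Nine of the eleven are clinical indicators. Two of these are day counts: "Fever: number of days body temperature ≥38" and "Pain score: number of days Numeric Rating Score ≥7". A neighbouring item carries an onset restriction: "Pressure sore developed during admission". On the observation window the section says "All indicators cover a period of maximum one month after discharge", which gives an end but no start. Fever and pain come from chart review: "Information about the other indicators will be retrospectively derived from patient medical records".

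On the design: "A multicenter non-randomized matched-controlled study is performed in The Netherlands". Control wards are matched on specialism and hospital type. On eligibility: "Exclusion criteria at patient level are: 1) Patients younger than 18 years; 2) Terminally ill patients; 3) Patients in daycare". Nothing there removes patients who arrive with fever, infection or severe pain.

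The Confounders section lists, among other patient covariates, primary diagnosis, co-morbidities, elective or emergency admission, and health-related quality of life at admission. Temperature and pain score at admission are not listed. The Data analyses section keeps a covariate in the final model only if it moves the coefficient for the ward care model by more than 10%.

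**The concern.** A patient admitted with pneumonia or a fracture may contribute fever days or severe-pain days that began before any hospitalist on the ward could act. If one arm takes more such patients, its wards show more fever or pain days even when care is the same. Conversely, a real difference in ward-onset fever may be diluted by days that belong to the presenting illness. A difference on either indicator, or the lack of one, would then be hard to attribute to the PA/MD model.

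**Working it through.** The document states no figure for fever or pain days, so there is no plan figure to reproduce. The check compares the definitions and then illustrates the possible size for fever.

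**1. Definitions side by side.** Seven of the nine clinical indicators record something that can happen only after admission: in-hospital death, unplanned transfer to intensive care, resuscitation, a pressure sore arising during the stay, hospital infection, emergency presentation after discharge, and non-elective readmission. Fever days and severe-pain days are the only two that can already be positive on arrival, and neither has an onset restriction.

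**2. What the plan does about case mix.**

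| Safeguard | What it covers | What it leaves |
|---|---|---|
| Matching on specialism and hospital type | Broad medical or surgical mix within each pair | Differences in severity or presentation within a specialism |
| Primary diagnosis, co-morbidities, admission type | Much of the reason for admission | Whether this patient had fever or severe pain on arrival |
| EQ-5D at admission | A pain item with three levels | No temperature; a coarse stand-in for a score of 7 or more |
| 10% change rule | Keeps proxies that move the coefficient materially | Can drop the others; cannot keep a variable that is not on the list |

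**3. Share of counted fever days that belong to arrival fever.** Let a be the proportion febrile on arrival with mean duration d1, and n the proportion with new fever with mean duration d2. Then share = a·d1 / (a·d1 + n·d2). All inputs are assumptions: a from 5% to 30%, n from 5% to 20%, durations of 1 or 2 days.

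- Lowest: 0.05×1 / (0.05×1 + 0.20×2) = 0.05/0.45 = 11%.
- Highest: 0.30×2 / (0.30×2 + 0.05×1) = 0.60/0.65 = 92%.
- A middle case (15% on arrival, 10% new, 2 days each): 0.30/0.50 = 60%.

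**4. Contrast from case mix alone.** In the middle case the mean is 0.15×2 + 0.10×2 = 0.50 days per patient. With identical care and no adjustment, an imbalance between arms in arrival fever adds:

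| Imbalance | Added days per patient | Relative to 0.50 |
|---|---|---|
| 2 points | 0.02×2 = 0.04 | 8% |
| 5 points | 0.05×2 = 0.10 | 20% |
| 10 points | 0.10×2 = 0.20 | 40% |

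**5. Dilution.** In the same case, suppose care cuts ward-onset fever by 20%. If it has no effect on arrival fever, the all-days count falls by 0.20×0.20/0.50 = 8%. If it shortens arrival fever by 20% as well, the count falls by the full 20%. The document does not say where in this range the truth lies.

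**The case against.** The strongest reply has four parts.

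- **Days after arrival partly reflect care.** The indicators count days from the hospital record. How long fever or severe pain lasts depends partly on treatment, so these days are not simply baseline. This stands, and more so for pain: severe-pain days in a patient with a fracture are a plausible measure of pain control. It is a reason to keep the all-days counts and adjust for the starting value.
- **Matching and adjustment are planned.** Pneumonia and fracture are primary diagnoses, and primary diagnosis is a listed covariate. A proxy that confounds materially would probably pass the 10% rule. This stands in part. The contrasts in step 4 are unadjusted and are upper illustrations, but the direct baseline values are not candidates for the model at all.
- **Hospital infections are a separate indicator**, so fever need not duplicate them. This is fair, but it does not remove the case-mix component from the fever count.
- **This is a condensed article.** The counting window and abstraction rules may be in the full protocol or in the inspectorate set from which the indicators come. The unstated start of counting is therefore not held against the plan. The covariate list, however, is set out in the article as predefined.

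A reader might go further and conclude that these indicators mostly measure why patients were admitted, or that days are counted from the moment of admission. The documents support neither. They give no rates of arrival or ward-onset symptoms, the illustrative share falls on both sides of one half, and no start of counting is stated. Nor does it follow that early days should be discarded. Dropping two days of the assumed 7-day average stay loses 2/7, about 29%, and would remove early postoperative pain that was not present on arrival.

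**Conclusion.** The point holds in a limited form. As defined, both indicators combine symptoms present on arrival with symptoms arising on the ward, in a non-randomized comparison that includes emergency admissions. The planned safeguards lessen the resulting bias between arms but work through proxies, and adjustment by itself does not change what is counted. The size is unknown: the 11% to 92% range and the 0.04 to 0.20 day contrasts rest entirely on assumed rates and were worked for fever only. The case is stronger for fever than for pain. It concerns two of eleven secondary indicators; length of stay, the primary outcome, is not touched.

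**What to change.** Extract temperature and numeric pain score on the day of admission from the records already being reviewed, and add both to the predefined patient covariates. Adjust the fever indicator for admission temperature and the pain indicator for admission pain score whether or not they meet the 10% rule. Keep the all-days counts as defined, and do not drop the first two days. Report fever days among patients without fever on admission as a supplementary ward-onset analysis.

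The cost is two more values to extract per patient. Some admission pain scores will be missing; the multiple imputation already planned can handle them, and their number should be reported by arm.
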